## Abstract

**Background:**

The efficacy of pericardium 6 (P6) acupoint stimulation to reduce the incidence of postoperative nausea and vomiting (PONV) has been proven in several randomised controlled clinical trials. However, little is known about the effectiveness in daily practice and its use in combination with traditional pharmacologic approaches.

**Methods:**

The primary objective of the P6NV study is to determine whether intraoperative acustimulation (acupuncture or acupressure) at the point P6 provides additional benefit when applied along with customary prophylactic intravenous antiemetics administered according to the local standard operating procedures (SOP). The primary endpoint is the incidence and severity of PONV within the first 24 h postoperatively reported with a validated postoperative nausea and vomiting intensity scale. The patient-reported outcome of perioperative quality of life (using the PPP33-questionnaire) and the detection of antiemetic-related side effects as well as the severity of PONV (via a standardised questionnaire) are secondary study objectives. P6NV is a national, multicentre, randomised, prospective, patient- and examiner-blinded interventional study and will be performed on 3500 adult patients with ASA classification I–III undergoing elective surgery under general anaesthesia and hospitalised for at least 24 h. Participating anaesthesiologists commit themselves to administer customised conventional antiemetic prophylaxis according to the local SOP by signing a statement before randomisation. The intervention group receives bilateral acupuncture or acupressure at P6. The control group receives no intervention. Before extubation, acustimulation is removed.

**Discussion:**

Since P6 acustimulation is performed by a wide range of anaesthesiologists receiving written and verbal information on acustimulation beforehand, this trial will provide information on the effectiveness of an ad hoc implementation of P6 stimulation techniques in anaesthesia departments using traditional pharmacologic PONV prophylaxis.

**Trial registration:**

DRKS DRKS00015272. Registered on August 15, 2018.

**Supplementary Information:**

The online version contains supplementary material available at 10.1186/s13063-022-06369-8.

## Administrative information

Note: The numbers in curly brackets in this protocol refer to SPIRIT Checklist item numbers. The order of the items has been modified to group similar items (see http://www.equator-network.org/reporting-guidelines/spirit-2013-statement-defining-standard-protocol-items-for-clinical-trials/).

## Introduction

### Background and rationale {6a}

Postoperative nausea and vomiting (PONV) is a frequent side effect of general anaesthesia. The incidence of PONV in untreated patients ranges from 10% (Apfel Score 0) up to about 80% (Apfel Score 4) [1, 2]. Often referred to as a big ‘little’ problem [3], severe PONV can result in major medical complications (e.g. wound dehiscence, aspiration of gastric contents, oesophageal rupture, pneumothorax, subcutaneous emphysema, and loss of vision [4, 5]). PONV is a leading cause of dissatisfaction with anaesthesia [6–8]. Not surprisingly, patients are willing to pay up to US $100 for a completely effective therapy [9–11]. Furthermore, it can be an economical issue due to a prolonged stay in the recovery room after surgery, further antiemetic medication, extra nursing time, delays in discharge, and, finally, unplanned readmission in the outpatient setting [11–14].

Administering antiemetic drugs avoiding volatile anaesthetics [15] and nitrous-oxide effectively reduce the incidence of PONV. These effects are additive [16]. A Cochrane review found evidence that pre- and intraoperative stimulation at pericardium 6 (P6) compared to a dummy procedure is also an effective intervention for preventing PONV [17]. There are also a few studies comparing acupuncture at P6 to a single antiemetic drug (e.g. dexamethasone [18], prochlorperazine [19]), showing positive results of P6.

The consensus guidelines for the management of PONV also suggest acupoint stimulation for the prophylaxis of PONV. However, little is known about the effectiveness in daily practice and the usefulness of this therapeutic option being used along with conventional pharmacologic approaches to prevent postoperative nausea and vomiting [20].

### Objectives {7}

We designed this pragmatic clinical trial to provide evidence whether ad hoc implementation of techniques for P6 acustimulation is effective to improve conventional pharmacologic prophylaxis administered on a customary basis in accordance with local standard operating procedures (SOP) in adult inpatients undergoing elective surgery.

### Trial design {8}

The study is designed as a multicentre, randomised, prospective, patient- and observer-blinded interventional trial.

## Methods: participants, interventions, and outcomes

### Study setting {9}

The study is conducted after positive follow-up votes from the ethics committees of the participating hospitals following a positive vote from the leading ethics committee of the Philipps-University of Marburg (chairman: [name]. [name]; approved on March 6, 2018 (Az.209/17)). The trial was registered at DRKS with the identifier: DRKS00015272. The study protocol will be performed in accordance with the Declaration of Helsinki and the ICH-GCP guidelines.

Participating clinics are intended to be representative of the German hospital landscape. Currently, five hospitals recruit patients to this study (one university hospital, one clinic of maximum treatment, three clinics of standard care, full list available from the authors). One main goal was to reduce interference with routine care for patients in participating centres as much as possible. A full list of study sites can be obtained from the sponsor.

### Eligibility criteria {10}

#### Inclusion criteria

The following are the inclusion criteria:18 years of age or olderAbility to participate in the postoperative assessment for PONVScheduled for general anaesthesiaInpatients expected to be hospitalised for at least 24 h after surgery

#### Exclusion criteria

The following are the exclusion criteria:Pregnancy and/or lactationExpected need for postoperative ventilation and/or intensive careAntineoplastic therapy, chemotherapy, or radiotherapy within the past 4 weeks for patients experiencing preoperative nausea

Reasons for dropout will include retraction of patient’s consent before or during participation, unexpected transfer to intensive care unit with intubation, ventilation, and sedation during follow-up.

### Who will take informed consent? {26a}

Patients are addressed in the preoperative assessment clinic and are provided with information on the aim of the study by the anaesthesia staff of participating clinics.

### Additional consent provisions for collection and use of participant data and biological specimens {26b}

Informed written consent is obtained from all participating patients meeting all inclusion and none of the exclusion criteria.

### Interventions

#### Explanation for the choice of comparators {6b}

Because of the nature of the intervention (acustimulation), no intervention will be performed in the control group.

#### Intervention description {11a}

##### Preparation for anaesthesia

The study protocol does not interfere with the preoperative preparation of patients. Consequently, patients may receive routine oral premedication the evening before and the morning of the surgical procedure. After entering the operating theatre, the usual procedures are performed (e.g. WHO Safety Checklist, standard monitoring, iv catheter). Induction and maintenance of anaesthesia are performed according to routine practice. All drugs administered due to the surgical procedure (e.g. premedication, induction agents, opioids, muscle relaxants) are recorded with their dosages and route of application, respectively.

##### Pharmacological antiemetic prophylaxis

The study aims to identify the effectiveness of P6 acustimulation along with conventional antiemetics administered intraoperatively. Thus, there is a high risk of bias that techniques for P6 stimulation might interfere with the pharmacological measures against PONV and vice versa. Special efforts are undertaken to ensure unbiased and comparable use of antiemetics in both groups. Comprehensive information is provided to the anaesthesiologists which highlight the need for ‘usual care’ in both groups. Additionally, all anaesthesiologists are required to fill in a document for personal ‘self-commitment’. With this form, the anaesthesiologist determines and documents the antiemetic prophylaxis that is suitable and will be administered to the individual patient (for the form, see Additional file 1). This part of the documentation form is filled out and signed by the anaesthesiologist and the attending nurse (four-eyes principle) before group allocation is revealed. This allows the determination of pharmacological interventions against PONV independent of the result of the randomisation procedure.

##### Antiemetic medication

The anaesthesia staff administers antiemetics according to their self-committed individual medication plan. One of a combination of the following measures may be used:▪ Dexamethasone 4–8 mg▪ 5-HT3-antagonists (e.g. ondansetron 4–8 mg, granisetron 1 mg)▪ Droperidol 0.5–1.5 mg▪ Haloperidol 0.5–1.5 mg▪ Metoclopramide 10–20 mg▪ Dimenhydrinate 50–70 mg▪ Fosaprepitant (no dose restriction)▪ Use of propofol for total intravenous anaesthesia▪Omission of nitrous oxide

The attending anaesthesiologist is free to administer any of the above-mentioned interventions and to combine drugs of different pharmacologic classes (e.g. due to high individual risk of the patient for PONV) but also to withhold antiemetic medication (e.g. if a low risk for PONV is present). Furthermore, the time of administration can be chosen by the overseeing anaesthesia team. The chosen prophylaxis (drug(s), dose, and time of administration) is recorded in a paper-based case report form (CRF).

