### Sample size {14}

Sample size calculation assumes a baseline incidence of PONV of 25%. This number is lower than reported in surveys on PONV with 29% [25] but considers routine pharmacological prophylaxis, at least in patients with increased risk for PONV.

A Cochrane review by Anna Lee [17] suggests that P6 stimulation can reduce PONV by approximately 30% (relative risk reduction), leading to a PONV-incidence in the treatment group of 17.5%. The trial is powered to detect an absolute reduction of 5% points (from 25 to 20%). This conservative estimation of P6 treatment considers that efficacy will not be as perfect as in efficacy trials, e.g. due to inconsequent or erroneous administration of the P6 stimulation. Power analysis was performed with PASS 2002 (Number cruncher software) and revealed that 1503 patients provide a power of 80% to detect an absolute 5% point difference with a type I error of 5% using the two-sided Fisher’s exact test. With an added safety margin of about 15% compensating for dropouts, etc. 2 × 1750 patients must be included.

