### Methods in analysis to handle protocol non-adherence and any statistical methods to handle missing data {20c}

Calculations will be performed as intention-to-treat analysis and per-protocol analysis. Imputation with the EM algorithm using the R-package ‘Amelia’ will be performed after missing data analysis.

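### The all-patient comparison answers the usual-care question, but not the narrower claim of benefit on top of administered antiemetics; the pre-allocation plan that could answer it is not used

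*Protocol article*

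**What the plan says.** The aim is worded in more than one way. The abstract asks whether P6 "provides additional benefit when applied along with customary prophylactic intravenous antiemetics administered according to the local standard operating procedures (SOP". The section on pharmacological antiemetic prophylaxis is the most literal: "The study aims to identify the effectiveness of P6 acustimulation along with conventional antiemetics administered intraoperatively". Objectives {7} is broader and pragmatic, asking whether ad hoc P6 stimulation "is effective to improve conventional pharmacologic prophylaxis administered on a customary basis in accordance with local standard operating procedures (SOP".

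The eligibility criteria require neither planned prophylaxis nor a minimum PONV risk. Under Antiemetic medication, the anaesthesiologist may choose and combine measures, "but also to withhold antiemetic medication (e.g. if a low risk for PONV is present". The listed measures include propofol-based total intravenous anaesthesia (TIVA) and omission of nitrous oxide as well as drugs. Sample size {14} recognises the mix: its 25% baseline "considers routine pharmacological prophylaxis, at least in patients with increased risk for PONV".

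The planned prophylaxis is written down and signed "before group allocation is revealed". On analysis sets, the protocol says "Calculations will be performed as intention-to-treat analysis and per-protocol analysis"; neither set is described as limited to patients with planned prophylaxis. The additional analyses {20b} plan a logistic regression on group, preoperative risk and administered antiemetic medication.

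**The concern.** In patients with an antiemetic planned, the randomised contrast is P6 plus drug against drug. In patients with none planned, it is P6 against no P6 without an antiemetic drug. The overall difference averages the two, so an overall result cannot simply be read as the effect in either group. A significant result could arise with no effect on top of drugs, and a real effect on top of drugs could be diluted.

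The regression does not settle this as written. Administered medication is fixed after the team has opened the envelope. The protocol itself warns of a high risk of bias from P6 and drug use influencing each other, and it expects documented deviations from the committed plan. Groups defined by what was given may therefore no longer be comparable between arms. Groups defined by the signed plan would be.

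**Working it through.** **1. The plan's own figure.** Inputs from Sample size {14}: 25% vs 20%, two-sided 5%, Fisher's exact test, 1503 patients for 80% power. The figure is read as per arm, because it leads to 2 × 1750. The normal formula for 80% power gives 1094 per arm, or 1134 with continuity correction; exact Fisher power at 1134 is 80.1%. At 1503 per arm, exact Fisher power is 90.0%. So 1503 matches 90% power, not the stated 80%. That is a separate matter, but it gives the starting point below: 91% by the uncorrected normal formula.

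**2. Two-stratum model.** Let f be the share with no antiemetic drug planned and q the control PONV rate in that share. The document gives neither. Assumed: f = 20–50% and q = 10–25%. The lower q is the untreated rate for Apfel score 0 in the Background; the upper is the trial's overall baseline. The overall control rate is held at 25%, so the control rate with a drug planned is p_d = (0.25 − f·q)/(1 − f).

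Power = Φ[(d − 1.96·SE0)/SE1], with n = 1503 per arm, d the overall difference, SE0 the pooled and SE1 the unpooled standard error. It is the chance of significance in favour of P6; with no effect anywhere it is 2.5%.

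**3. Scenario A: no effect with drugs, 30% relative reduction without** (the review figure cited in the sample size section). d = 0.30·f·q. Example: f = 0.5, q = 0.25 gives d = 0.0375.

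| f | q = 10%: d, power | q = 25%: d, power |
|---|---|---|
| 20% | 0.6 points, 6% | 1.5 points, 16% |
| 30% | 0.9 points, 8% | 2.25 points, 30% |
| 40% | 1.2 points, 12% | 3.0 points, 49% |
| 50% | 1.5 points, 16% | 3.75 points, 68% |

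The full 5-point difference would need f = 0.05/(0.30·0.25) = 67% at q = 25%. It is impossible at q = 10%, where f would have to be 167%.

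**4. Scenario B: 20% relative reduction with drugs, none without.** d = 0.20·(1 − f)·p_d = 0.20·(0.25 − f·q). The committed-drug stratum has about 1503·(1 − f) per arm and compares p_d with 0.8·p_d. Example: f = 0.4, q = 0.25 gives 25% vs 22% overall and 25% vs 20% with 902 per arm in the stratum.

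| f | q = 10%: overall / stratum | q = 25%: overall / stratum |
|---|---|---|
| 20% | 85% / 90% | 74% / 84% |
| 30% | 82% / 89% | 62% / 79% |
| 40% | 78% / 89% | 49% / 72% |
| 50% | 74% / 90% | 36% / 64% |

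In this scenario the stratum test has the higher power in every cell, despite fewer patients.

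**5. Room for the stratum analysis.** For 25% vs 20% in the committed-drug stratum, 80% power needs 1134 evaluable per arm with continuity correction. From 1503, that holds while f is at most 1 − 1134/1503 = about 25%.

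**The case against.** The strongest reply is that the trial asks a policy question and enrols the population for it. Objectives {7} calls the trial pragmatic and refers to customary care under local procedures. The Discussion speaks of individually tailored treatment and of transferring results to the largest possible population. Withholding a drug at low risk is part of such care, and the sample size section says so. This stands: for that question, all patients belong in the primary analysis.

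A reader might infer that patients without a drug are compared on P6 alone against nothing, and that this is already known to work. The documents do not support that. TIVA and omission of nitrous oxide are listed as prophylactic measures, so a patient without a drug may still have committed prophylaxis. The cited review compared P6 with a dummy procedure, and the protocol says little is known about effectiveness in daily practice.

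It is also fair that the regression is planned and touches the question. Whether it contains an interaction, and which strata are reported, may properly be left to the SAP. What remains is that the protocol names the post-allocation variable.

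Finally, the upper ends of the ranges need both a large no-drug share and a PONV rate in it near 25%. The protocol's example for withholding is low risk, which points to the lower rates. It is only an example, and no cap or expected share is given.

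**Conclusion.** The point holds in a limited form. The overall comparison is valid for P6 on top of customary care. It does not by itself support the narrower statement, in the abstract and the prophylaxis section, of benefit along with administered antiemetics, and the one related analysis conditions on a variable settled after allocation is revealed.

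Under the assumed shares and rates, a significant overall benefit with no add-on effect has a chance of 6–68%. Power for an effect confined to drug-treated patients is 36–85% overall against 64–90% in the committed-drug stratum. If withholding is confined to patients at about the 10% rate, these become 6–16%, and 74–85% against about 90%, which is modest. The stronger conclusions, that enrolling these patients is a design error or that a positive result would probably come from them alone, do not follow from the documents.

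**What to change.** - Keep all patients, by intention to treat, as the primary pragmatic analysis.
- In the additional analyses {20b}, replace administered with self-committed prophylaxis as the grouping variable.
- Pre-specify the treatment effect, by intention to treat, in patients whose signed plan lists at least one antiemetic drug.
- Report alongside it the stratum with no committed drug, showing separately those with only TIVA or nitrous oxide omission, and the interaction between group and committed prophylaxis.
- State that any add-on conclusion is drawn from the committed-drug stratum, and align the wording of the aim in the abstract and the prophylaxis section with Objectives {7}.

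The cost is wording in the protocol and SAP. The variable is already collected before allocation, and neither care nor recruitment changes. The downside is that the add-on estimate rests on fewer patients and is less precise. For 25% vs 20%, its power falls below 80% once the no-drug share exceeds about a quarter of 1503 evaluable patients per arm.

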##### Intervention

The anaesthesia team is allowed to open the opaque randomisation envelope after completing the self-commitment. This envelope includes information whether the patient is allocated to the control or the intervention group.

Patients allocated to the intervention group receive acustimulation at both forearms at the P6 point immediately after the induction of anaesthesia. Pressure is applied to the needles for about 15 s at the beginning and the end of the intervention to stimulate P6. The applied force should cause the needle tip to reach a depth of 0.5 to 1 cun (traditional Chinese measuring unit) [21]. Anaesthesiologists can also use acupressure bands for intervention instead of acupuncture needles. The intervention and its duration of administration are recorded.

The control group receives only the designated antiemetic prophylaxis according to the self-commitment.

The P6 acupoint is located 2 cun [22] from the distal palmar crease between the flexor carpi radialis tendon and the palmaris longus tendon on the volar surface of both forearms [23]. All anaesthesiologists were informed about the study and were provided with verbal and written information on anatomical location of the P6 stimulation point and the need for applying pressure to the needle. An information sheet (including the illustration from Fig. 1) was available in all operating rooms. For acupuncture, Seirin® New Pyonex needles with a length of 1.5 mm will be used. Acupressure is performed with GoTravel Acustrap bands.

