### Assignment of interventions: blinding

#### Who will be blinded {17a}

This study is designed patient- and observer-blinded. The intervention is applied only during the maintenance of general anaesthesia. Thus, the patient remains blinded to the intervention. All patients receive opaque dressings on the intervention sites on both forearms. The patient’s group assignment and intervention remain hidden from the PACU nurses as they gather the primary endpoint as well as the staff that collects data during the follow-up. Data analysis will be performed blinded as well.

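### The envelope may be opened once the self-commitment is complete, with no link to induction, so allocation may be known beside an awake patient and before uncommitted induction drugs and opioids are given

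*Protocol article*

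**What the plan says.** Four parts of the protocol article bear on this point.

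- **When allocation is revealed.** Under Pharmacological antiemetic prophylaxis, the self-commitment form is "signed by the anaesthesiologist and the attending nurse (four-eyes principle) before group allocation is revealed". Under Intervention: "The anaesthesia team is allowed to open the opaque randomisation envelope after completing the self-commitment". Neither place gives a clock time or refers to induction.
- **What the form fixes.** On it, "the anaesthesiologist determines and documents the antiemetic prophylaxis that is suitable and will be administered to the individual patient". The measures listed under Antiemetic medication include the antiemetic drugs, "Use of propofol for total intravenous anaesthesia" and omission of nitrous oxide. The time at which antiemetics are given is left to the team. Under {11c}, deviations from the plan are documented with a reason.
- **What the form does not fix.** Under Preparation for anaesthesia: "Induction and maintenance of anaesthesia are performed according to routine practice". Induction agents, opioids and other drugs are recorded with dose and route.
- **When allocation is needed, and how blinding is argued.** Patients in the intervention group "receive acustimulation at both forearms at the P6 point immediately after the induction of anaesthesia". Section {17a} says: "The intervention is applied only during the maintenance of general anaesthesia. Thus, the patient remains blinded to the intervention". It adds opaque dressings on both forearms and keeps assignment hidden from PACU nurses and follow-up staff.

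**The concern.** The rule allows the allocation to be known earlier than any described step requires. Two of the committed items, propofol-based anaesthesia and omission of nitrous oxide, are choices of anaesthetic technique, so the form can be expected to be completed before induction. From that moment the envelope may be opened. Stimulation follows directly on induction, which gives a busy team a practical reason to open it early and prepare needles or bands.

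Two things are then less well protected than they could be.

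1. **Patient blinding.** Section {17a} infers it from the intervention being confined to anaesthesia. That covers what is done to the patient, but not what an awake patient may see or hear beforehand. The primary endpoint includes nausea, and patients complete the PIS themselves on the first postoperative day.
2. **Drug choices at induction.** Induction agents and opioids may be chosen by staff who already know the arm. The protocol itself warns of a high risk of bias from P6 stimulation and pharmacological measures influencing each other, and its Limitations section names postoperative opioids as an emetogenic stimulus.

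**Working it through.** **Step 1: order of events, from the text.**

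| Event | Earliest time the protocol allows or states |
|---|---|
| Self-commitment signed by two people | Before allocation is revealed; no time relative to induction |
| Envelope opened | As soon as the form is complete |
| Induction agents and opioids | Routine practice; not committed in advance |
| P6 stimulation | Immediately after induction |

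The interval from signing to the end of induction is the window in question. No described step within it needs the allocation.

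**Step 2: what is open in that window.**

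- Listed antiemetics, propofol-based anaesthesia and nitrous oxide: fixed before opening, with deviations documented. Protected.
- Induction agents and opioids: recorded only. Exposed.
- Time of antiemetic administration: left to the team. Exposed, but not only in this window.
- Disclosure to the patient: not addressed before induction. Possible, not shown.

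**Step 3: sensitivity illustration only.** This shows how sensitive the trial is to a small one-sided change in co-treatment. It is not an estimate of the bias that the fix would remove.

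*Inputs from the Sample size section:* control rate 25%, treated rate 20%, two-sided 5%, and 1503, read as per arm because the total is given as 2 × 1750.

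*Assumptions, not in the document:* a share x of one arm, 10% or 20%, receives an added choice with a PONV relative risk RR of 0.70 to 0.80.

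*Method:* sum over both binomial distributions with the continuity-corrected two-proportion test, which is close to Fisher's exact test.

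*Plan's own figure first:* 25% against 20% with 1503 per arm gives power 90.0%, not the declared 80%. At 80% power, the continuity-corrected formula needs 1134 per arm; 1504 is the 90% figure. That mismatch is a separate matter, but the illustration starts from 90%.

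*Shifted rate:* 0.25 × [1 − x(1 − RR)]. For x = 0.10 and RR = 0.70 this is 0.25 × 0.97 = 24.25%. For x = 0.10 and RR = 0.80 it is 0.25 × 0.98 = 24.5%. For x = 0.20 the rates are 23.5% and 24.0%.

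| Share x | Power if controls are shifted (treated rate 20%) | Type I error if the P6 arm is shifted (no true effect) |
|---|---|---|
| 0 | 90.0% | 4.5% |
| 10% | 79.0% to 83.3% | 5.6% to 7.0% |
| 20% | 62.6% to 74.0% | 9.0% to 15.0% |

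Against a target difference of 5 points, shifts of 0.5 to 1.5 points are not negligible. The calculation does not say how large the shift is, nor how much of it would arise before the end of induction.

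**The case against.** The case on the other side is substantial.

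- **The main safeguard is already in place.** The prophylaxis is fixed and countersigned before allocation is revealed, it covers the PONV measures that the protocol names, and deviations must be explained. This stands and narrows the point to what the form does not cover.
- **Disclosure to the patient is not shown.** A reader might infer that patients are unblinded. The document does not support that. It permits early opening without directing it, says nothing about telling or showing the patient, and adds dressings in both arms. Knowledge held by staff is not knowledge held by the patient.
- **The endpoint is not purely patient-reported.** It includes retching, vomiting and antiemetic need, and blinded PACU nurses gather part of it. This stands.
- **The illustration does not measure the gap.** A reader might take the fall in power or the 15% false-positive rate as the effect of early opening. They are not. The relative risks and shares are assumed, no uncommitted choice of that strength is identified in the document, and an added antiemetic would breach the signed plan. Co-treatment can also change during maintenance, when the team knows the arm whatever the opening rule. The 10% scenario still leaves power at about the declared 80%.
- **The exact moment may be set in site instructions.** An article condenses. But this article does state an operative rule, and the rule as stated allows early opening.
- **The change is not free.** Preparation moves into the period just after induction, when stimulation is due at once, and the trial aims to interfere little with routine care. The cost is small but not nil.

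**Conclusion.** The point holds as a modest design weakness. As written, the rule allows allocation to be known before induction, while nothing described before induction needs it, and section {17a} rests patient blinding on the timing of the intervention alone. The exposure is limited to possible disclosure to an awake patient and to uncommitted choices up to the end of induction.

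Its size is unknown. The document gives neither the usual time of opening nor a bias estimate, so the power and type I error figures serve only as a sensitivity illustration under stated assumptions. The conclusion rests on the text: no section links opening to induction, and induction drugs and opioids fall outside the self-commitment. It does not rest on any evidence that early opening or disclosure occurs. Sample size is unaffected.

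**What to change.** In the Intervention section, replace the opening rule with wording such as: *The envelope is opened only after the self-commitment has been signed and anaesthesia has been induced. The time of opening is recorded in the CRF.* In section {17a}, base patient blinding on this rule as well as on the timing of the intervention. Recruitment is under way according to the Trial status section, so a site instruction can apply the rule to the remaining patients.

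One practical point: section {16b} puts the case report form in the same envelope as the allocation. The current rule already requires the form to be signed before allocation is revealed, so the two must already be separable and no new burden arises.

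Cost: one added instruction, one CRF field and a short delay before stimulation; no extra patients. Limit: the team still knows the arm during maintenance, so later opioid and anaesthetic decisions stay exposed and co-treatment is only partly protected. The recorded opening time would at least make adherence to the rule checkable.
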